### Primary Outcome Measurement

The fMRI examination will be performed in the Imaging Department of the Rehabilitation Hospital affiliated to Fujian University of Traditional Chinese Medicine. The first fMRI scan will be performed 1 day before the start of treatment, and the second fMRI scan will be performed within 6 hours after the last intervention. The fMRI data will be collected by a 3.0 Tesla magnetic resonance scanner (MAGNETOM Prisma 3.0T, Siemens) with 64-channel phase-array head coils. During the acquisition process, participants will be required to close their eyes, relax, stay awake, keep their heads fixed as far as possible, and not perform thinking activities. We will perform fMRI at the beginning and end of the experiment.

To acquire the structural images, we will use the following parameters. The T1-weighted imaging scan parameters are as follows: time of repeat=2200 ms, time of echo=2.48 ms, flip angle=8°, field of view=230 mm×230 mm, matrix=256×256, resolution=0.98×0.98×1 mm^3^, slice number=160, and slice thickness=1.0 mm. The functional images will be acquired using the following parameters: time of repeat=2000 ms, time of echo=30 ms, flip angle=90°, field of view=230 mm, matrix=64×64, resolution=3.6×3.6×3.6 mm^3^, slice number=37, slice thickness=3.6 mm, and scan time=10 minutes for 300 timepoints.

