### fMRI Data Preprocessing

First, MRIConvert 2.0 software (Lewis Center for Neuroimaging) converts the DICOM format of the fMRI images into a Neuroimaging Informatics Technology Initiative format file for data analysis. Next, we apply the default preprocessing pipeline in the Statistical Parametric Mapping–based CONN 2.0b toolbox of the MATLAB 2022b (The MathWorks, Inc) platform to preprocess all the nuclear magnetic data.

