### Statistical Analysis

Statistical analysis will be conducted using SPSS 26.0 statistical software. Count data will involve the ratio of the sex and age variables compared between the 2 groups via the *χ*^2^ test of the 4-fold table or the Fisher test. The SF-MPQ scores, PPTs, and ODI scores are the rank data. Therefore, the Mann-Whitney *U* test will be used for the intergroup comparison, and the Wilcoxon symbolic test will be applied for the intragroup comparison. Paired 2-sided *t* test will be used to assess the difference in ALFF and ReHo between the 2 groups. In addition, Pearson correlation coefficients will be used to estimate the connection between the seed region and all of the voxels within the whole brain separately based on the patients. Statistical significance will be set at *P*<.05 (2-sided).

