### Sample Size Calculation

There is still no consensus on sample size estimates for fMRI studies. Desmond and Glover’s [31] empirical research results indicate that to achieve 80% test power at the single voxel level in magnetic resonance imaging data with a multiple comparison correction threshold of 0.05, at least 24 participants are required. We also referred to similar studies investigating neuroimaging mechanisms related to LDH and combined them with the research design for this topic [12,18]. The visual analog scale was selected as an important indicator of LDH pain level [32]. According to literature [33], patients with LDH had a score of 4.28 (SD 1.16) points after Tuina intervention and a score of 5.68 (SD 1.26) points after traction intervention. We used G*Power 3.1 software to calculate the sample size based on the mean, wherein α is .05 and power is .85. Each of the 2 groups require 30 cases. With 20% dropout, 38 cases are required for each group for a total of 72 cases.

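### The t test named for ALFF and ReHo cannot adjust for head motion, and no check of motion by arm is stated, so a motion difference at the second scan could be read as a brain effect

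*Protocol article*

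**What the plan says.** Statistical Analysis fixes the group-level test for two of the primary imaging measures: a paired, two-sided t test "will be used to assess the difference in ALFF and ReHo between the 2 groups". It names no covariate. The 5% two-sided level is set in the same section.

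Two places bear on head motion:

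- Primary Outcome Measurement asks participants to "keep their heads fixed as far as possible" during a 10-minute functional run.
- fMRI Data Preprocessing says "we apply the default preprocessing pipeline in the Statistical Parametric Mapping–based CONN 2.0b toolbox". The steps of that pipeline are not given.

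No section states a motion covariate, a limit for excluding scans, or a comparison of motion between arms.

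Three further statements matter:

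- On timing, "the second fMRI scan will be performed within 6 hours after the last intervention" (Primary Outcome Measurement).
- On expected pain, Sample Size Calculation takes from the literature "a score of 4.28 (SD 1.16) points after Tuina intervention and a score of 5.68 (SD 1.26) points after traction intervention".
- FC Analysis takes regions that differ on ALFF or ReHo forward into the connectivity analysis. The closing Conclusions section expects pain relief to be tied to changed activity in pain-related regions.

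**The concern.** Participants have nerve-root pain and must lie still for 10 minutes. If more comfortable patients move less, an arm with better pain relief will move less at the second scan. If motion left after preprocessing also shifts ALFF or ReHo, the arms can differ on the primary measures without any direct effect of treatment on brain activity.

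Randomisation does not balance this, because motion at the second scan arises after treatment. A larger sample does not help either: the spurious difference stays the same while the power to detect it rises.

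The mechanism conclusion is at stake. Motion that follows pain relief would look like brain activity that follows pain relief, which is what the trial expects to find. A region picked out for this reason would also enter the connectivity analysis.

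**Working it through.** **No figure to reproduce.** The article gives no figure for head motion, so the check is a sensitivity calculation. (The printed sample size of 30 per arm does not follow from the pain figures used below, but that is a separate matter and does not bear on this point.)

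**Inputs from the document**
- Post-treatment pain score: 4.28 (SD 1.16) after Tuina and 5.68 (SD 1.26) after traction (Sample Size Calculation).
- 30 per arm before and 38 per arm after allowance for dropout (same section).
- Two-sided 5% level (Statistical Analysis).

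**Inputs assumed**
- *a*: within-arm correlation of pain with head motion at the second scan.
- *b*: within-arm correlation of motion with ALFF or ReHo after preprocessing.
- No direct effect of treatment on the imaging measure.

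**Step 1: pain gap in SD units.** Pooled SD = √((1.16² + 1.26²)/2) = 1.211. Difference = 5.68 − 4.28 = 1.40. Standardised gap = 1.40/1.211 = 1.156.

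**Step 2: spurious imaging difference.** Motion gap = 1.156 × *a*. Spurious standardised difference *d* = 1.156 × *a* × *b*.

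**Step 3: error rate of one test.** This uses an unadjusted two-sample t test with *n* per arm, noncentrality *d* × √(*n*/2) and 2*n* − 2 degrees of freedom. The two-sample form is used because a paired test cannot compare two independent arms.

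| *a* | *b* | *d* | Error rate, 30 per arm | Error rate, 38 per arm |
|---|---|---|---|---|
| 0 | any | 0 | 5.0% | 5.0% |
| 0.1 | 0.1 | 0.01 | 5.0% | 5.0% |
| 0.2 | 0.2 | 0.05 | 5.4% | 5.5% |
| 0.3 | 0.3 | 0.10 | 6.8% | 7.3% |
| 0.4 | 0.5 | 0.23 | 14.3% | 16.9% |
| 0.5 | 0.5 | 0.29 | 19.6% | 23.8% |

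Example for the fifth row at 38 per arm: *d* = 1.156 × 0.4 × 0.5 = 0.231, and the noncentrality is 0.231 × √19 = 1.01. At 30 per arm the noncentrality is 0.231 × √15 = 0.89.

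**Step 4: what the named test can do.** Neither a paired nor a two-sample t test has room for a motion term. The wording is itself at odds, since a paired test is named for a comparison between two separately randomised groups. If a before-after test within each arm was meant, the fall in pain from first to second scan takes the place of the gap between arms, and there is still no motion term.

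**The case against.** The strongest objection is that the article does not show motion to be uncontrolled. All images go through a default pipeline whose steps are not listed. It may include realignment, regression on motion parameters or flagging of outlier volumes, and a condensed article may leave such detail to a fuller protocol or analysis plan. This stands: a reader might infer that nothing is done about motion beyond the instruction to keep still, and the documents do not support that. Correction within each scan, however, does not show that the remaining motion is balanced between arms, and the stated group-level test can neither check nor adjust for it.

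A second objection is that the causal chain is assumed. No section links pain to motion, or motion to ALFF or ReHo. This also stands, and is why the range above runs down to no effect.

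A third is that the 1.156 SD gap should not be taken as the trial's forecast. The figures are literature values for traction alone, whereas the comparator here is TENS with traction, and the closing Conclusions section expects relief with Tuina without stating a difference between arms. The true gap could be smaller, and the error rates would fall with it.

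A fourth is that motion at the second scan is measured after randomisation and may be a result of treatment. Adjusting for it conditions on a possible mediator, and removing high-motion scans could remove more patients from one arm even if decided blind. This rules out a motion-adjusted model as the replacement main analysis. It does not count against reporting motion by arm or against adjustment as a sensitivity analysis.

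**Conclusion.** The point holds in a limited form. The stated group-level analysis of ALFF and ReHo has no motion term, no check of motion by arm is stated, and the results feed a mechanism claim. If residual motion differs between arms at the second scan, the analysis as written cannot separate it from a brain effect.

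The size is unknown. Under the assumptions shown, the error rate of a single test runs from 5% (no inflation) through the mid-teens to about 24% when both correlations are 0.5 at 38 per arm. These rates depend wholly on the two assumed correlations, on a pain gap borrowed from a different comparator and on an unadjusted two-sample test. It would go too far to say that motion will be reported as Tuina's mechanism; the documents support only that the plan, as stated, could not detect it if it happened.

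This is worth settling before analysis, which according to the abstract had not begun when the article was written.

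**What to change.** 1. Keep an unadjusted between-arm comparison of ALFF and ReHo as the main analysis, with a test for independent groups in place of the paired t test.
2. State which motion steps the default pipeline applies.
3. Compute mean framewise displacement for each scan from the realignment parameters and report it by arm and visit.
4. Pre-specify a sensitivity analysis of ALFF and ReHo by a linear model of arm plus mean framewise displacement.
5. Draw the mechanism conclusion only for regions that are consistent in both analyses.
6. If a motion limit for excluding scans is used, set it in advance, apply it blind to arm and report the counts by arm.

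**Cost.** Analysis time only; the motion values come from scans already planned. The downside is interpretive: because motion at the second scan may lie on the path from treatment to outcome, the adjusted result can be biased in either direction. It is a check on the main result, not a substitute for it. Any exclusion limit will also cost some scans, possibly more in one arm.

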### fMRI Data Processing

#### ALFF Analysis

The ALFF analysis will be performed using the AFNI (Analysis of Functional NeuroImages) software [27]. The fast Fourier transform transforms the filtered time series to the frequency domain (parameters: taper=0%, fast Fourier transform length=shortest) to obtain the power spectrum. Since the power of a given frequency is proportional to the square of the magnitude of this frequency component in the original time series, the square root is calculated at each frequency of the power spectrum, and the average square root ranges from 0.01 Hz to 0.08 Hz at each voxel. This average square root is considered as the ALFF.

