#### ReHo Analysis

The Kendall coefficient of concordance is used to measure the local synchronization of the time series of its nearest neighbor voxels as 
[figure not shown]

[28], where W is the Kendall coefficient of concordance among given voxels, ranging from 0 to 1; Ri is the sum rank of the ith timepoint; R (n+1) K/2 is the mean of Ri; K is the number of time series within a measured cluster (K=7, 19, and 27; K=27 is used in this study); and n is the number of ranks (here n=60). The Kendall coefficient of concordance program is coded in MATLAB [29]. Thus, an individual ReHo map is generated for each data set.

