#### FC Analysis

Differential brain regions obtained by ALFF or ReHo analysis, regions of interest, and differential brain regions will be selected, and FC will be calculated. An FC plot for each participant will be obtained by DynamicBC using the sliding window method. We will select a window length of 50 times of repeat (time of repeat: 100 seconds) with a window overlap of 98% (step size of 1 time of repeat) to calculate the FC for each participant. The FC plots for each participant will be calculated within each window to generate a series of FC plots. The coefficient of variation of the FC map is calculated to measure the temporal variability of intrinsic brain activity. Finally, the FC variability of all the participants will be transformed into standardized *z* scores to enhance the normality of the data by subtracting the mean of each voxel and dividing by the standard deviation [30].

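### The only significance rule given, P<.05 two-sided, carries no multiple-comparison correction, although the primary ALFF and ReHo comparisons are voxelwise and supply seeds for the FC analysis

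*Protocol article*

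**What the plan says.** Outcome Measurements makes fMRI the main outcome, and Primary Outcome Measurement schedules one scan before treatment and one after the last session. ALFF Analysis works voxel by voxel: "the average square root ranges from 0.01 Hz to 0.08 Hz at each voxel". ReHo Analysis produces a map: "an individual ReHo map is generated for each data set".

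Statistical Analysis names the test for both metrics, "Paired 2-sided *t* test will be used to assess the difference in ALFF and ReHo between the 2 groups". It adds that Pearson coefficients will serve to "estimate the connection between the seed region and all of the voxels within the whole brain separately based on the patients", and closes with "Statistical significance will be set at *P*<.05 (2-sided". SPSS is the only software named in that section. From fMRI Data Preprocessing to Statistical Analysis, no familywise, false-discovery-rate, cluster or permutation method appears.

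FC Analysis describes the next step: "Differential brain regions obtained by ALFF or ReHo analysis, regions of interest, and differential brain regions will be selected, and FC will be calculated".

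Correction is mentioned once, under Sample Size Calculation. There an outside empirical result is cited for 80% power at the single-voxel level, "with a multiple comparison correction threshold of 0.05, at least 24 participants are required".

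**The concern.** A threshold of .05 is a sensible criterion for one test on one clinical score. A voxelwise comparison runs tens of thousands of tests per map, and here there are two primary maps. If each voxel is judged at .05, about one voxel in twenty passes when nothing differs between the arms. The trial would then report regions that differ between Tuina and TENS with traction even if the two had identical effects on the brain. Because differential regions go on to seed the connectivity analysis, chance findings would also shape the second stage. The planned conclusion about a cerebral mechanism rests on those regions.

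**Working it through.** **1. What the plan itself calculates.** It gives no false-positive figure to reproduce. Its sample size uses a visual analog scale (VAS) comparison: 4.28 (SD 1.16) against 5.68 (SD 1.26), α = .05, power .85.
- Pooled SD = √[(1.16² + 1.26²)/2] = 1.211, so d = 1.40/1.211 = 1.156.
- This is a single test on a clinical score, so the trial's N is not tied to any imaging threshold, corrected or uncorrected.
- These inputs give 15 per group by an exact two-sided t test, not the stated 30. That is a separate point, and nothing below depends on it.

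**2. Number of voxels per map.** Primary Outcome Measurement gives functional voxels of 3.6 × 3.6 × 3.6 mm.
- Voxel volume = 3.6³ = 46.656 mm³.
- Assumed brain volume (not in the document): 1,200 to 1,500 cm³.
- Voxels = 1,200,000/46.656 = 25,720, up to 1,500,000/46.656 = 32,150.

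**3. Expected false positives in one null map at .05.**
- 25,720 × .05 = 1,286.
- 32,150 × .05 = 1,608.

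This expectation is not altered by correlation between neighbouring voxels. It needs only a test that holds its nominal 5% level. Naming a paired test for two independent groups is a separate matter.

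**4. A second assumption as a check.** The acquisition grid is 64 × 64 × 37 = 151,552 voxels. If 20% to 40% of it lies in the brain (assumed), there are about 30,310 to 60,620 voxels and 1,516 to 3,031 expected false positives. The order of magnitude is the same.

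**5. Chance of at least one false positive.** For m independent tests this is 1 − .95^m.

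| m | Familywise error |
|---|---|
| 10 | .40 |
| 50 | .92 |
| 100 | .994 |
| 200 | above .9999 |

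A whole-brain map would have to behave like far fewer than 50 independent tests before this risk became modest.

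**6. Spatial correlation.** Null maps were simulated with 30 per group, an ellipsoid of 31,100 voxels of 3.6 mm, and an independent two-sided t test at .05. Smoothness was assumed, since none is stated; 60 maps were run at each value.

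| Smoothness (FWHM) | Maps with false positives | Mean false-positive voxels | Mean number of clusters |
|---|---|---|---|
| 8 mm | 60 of 60 | 1,560 | 316 |
| 12 mm | 60 of 60 | 1,563 | 112 |

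The voxel counts agree with 31,100 × .05 = 1,555. With 60 of 60, the one-sided 95% lower limit for the familywise error is .05^(1/60) = .95. Smoothing gathers the false positives into fewer, larger clusters, which look more like real regions; it does not remove them.

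**7. Carry-forward.** FC Analysis takes differential ALFF or ReHo regions as a source of seeds. With false-positive clusters near certain in a null map, some seeds would be chance findings.

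**The case against.** The strongest reply is that the article omits a method and does not fix a wrong one. It nowhere says that maps will be uncorrected. A level of .05 is compatible with corrected inference; the outside result cited for sample size is itself expressed at a corrected .05. This is a condensed article, and cluster thresholds are often left to a fuller plan. The closing sentence follows an opening reference to SPSS, whereas the imaging steps use other software, so it may not have been meant as a map threshold.

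Much of this stands, and it limits what can be claimed. A reader might infer four stronger things that the document does not support:

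- **That the plan commits to uncorrected maps.** It is silent.
- **That the sample size relies on a corrected threshold which the analysis then drops.** The 24-participant result is background; N comes from the VAS comparison. The two sections sit awkwardly together, but they do not strictly contradict each other.
- **That every FC seed map will be group-tested at .05.** The Pearson sentence describes how seed-to-voxel maps are built. No between-group FC test is named, so the false-positive count is not extended to FC.
- **That all seeds come from differential regions.** Regions of interest are listed as well.

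What does not stand is that the matter is merely left open. The same paragraph that names the ALFF and ReHo test states the significance criterion, and it is the only one in the document. The article is detailed elsewhere on imaging: the ReHo neighbourhood size, the Fourier settings and the window overlap are all given. A later plan that added correction would be changing the published criterion for the primary outcome.

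**Conclusion.** The concern holds for the primary ALFF and ReHo comparisons. The only stated rule is P<.05 two-sided with no correction attached. If it is followed as written, false-positive regions are near certain: roughly 1,290 to 1,610 voxels per null map, with a familywise error near 100%.

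The count assumes a brain volume of 1,200 to 1,500 cm³ and the acquisition voxel size, because the grid after preprocessing is not given. It also reads the comparisons as whole-brain, because they are made on voxelwise maps and no region is prespecified for them. Other reasonable assumptions change the count (up to about 3,000) but not the conclusion. The finding concerns what the published rule would produce; it does not show that the investigators intend to leave the maps uncorrected.

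**What to change.** Amend Statistical Analysis to state that:

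- whole-brain ALFF and ReHo contrasts are judged at a corrected .05 level by one named, prespecified method, run in imaging software;
- the two primary metrics are allowed for, for example by .025 each;
- data-derived FC seeds come only from regions that survive this correction;
- any group test of FC maps uses the same correction;
- plain P<.05 applies to single clinical outcomes only.

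Cluster-level familywise control with a strict voxel-forming threshold such as P<.001, a permutation method, or false-discovery-rate control would each be acceptable. What matters is that one is chosen, and the error rate it controls is stated, before the maps are analysed. The abstract reports that no data analysis had been performed, so at that point this could still be prespecified.

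The change is wording only. The cost is that fewer regions will reach significance. As an illustration only, since no imaging effect size is given, take the VAS effect (d = 1.156) as the effect at a voxel:

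| n per group | Power at .05 | Power at .001 | Power at Bonferroni, 30,000 voxels |
|---|---|---|---|
| 30 | 99% | 84% | 23% |
| 38 | 99.9% | 94% | 45% |

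The loss therefore depends heavily on the method, which is a further reason to choose it in advance.

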### Sample Size Calculation

There is still no consensus on sample size estimates for fMRI studies. Desmond and Glover’s [31] empirical research results indicate that to achieve 80% test power at the single voxel level in magnetic resonance imaging data with a multiple comparison correction threshold of 0.05, at least 24 participants are required. We also referred to similar studies investigating neuroimaging mechanisms related to LDH and combined them with the research design for this topic [12,18]. The visual analog scale was selected as an important indicator of LDH pain level [32]. According to literature [33], patients with LDH had a score of 4.28 (SD 1.16) points after Tuina intervention and a score of 5.68 (SD 1.26) points after traction intervention. We used G*Power 3.1 software to calculate the sample size based on the mean, wherein α is .05 and power is .85. Each of the 2 groups require 30 cases. With 20% dropout, 38 cases are required for each group for a total of 72 cases.

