## Methods

### Trial Design

This is a single-center randomized controlled trial with 2 parallel arms: the Tuina intervention group and traction with transcutaneous electrical nerve stimulation (TENS) intervention group. A total of 76 eligible patients with LDH will be recruited for this trial, and patients with LDH will be randomly assigned to the groups in 1:1 ratio. All patients will provide written informed consent. Outcome evaluation and statistical analysis will be performed by 2 researchers who do not know the specific groups. The trial design flowchart is shown in Figure 1, and the study schedule is shown in Figure 2. This study will be conducted in the Rehabilitation Hospital affiliated to Fujian University of Traditional Chinese Medicine. This study follows the CONSORT (Consolidated Standards of Reporting Trials) guidelines (Multimedia Appendix 1).

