### Outcome Measurements

We will present the trial results by using both objective and subjective indicators. fMRI will be used for the main measurements, reflecting the changes in the participants’ brain structure and functional changes. Short-Form McGill Pain Questionnaire (SF-MPQ), pressure pain thresholds (PPTs), and the Oswestry disability index (ODI) will indicate the degree of pain and lumbar dysfunction and will be used for secondary outcome measurements.

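### The sample-size figures do not follow from their own inputs: the cited VAS data need 15 per group, not 30; two groups of 38 make 76, not 72; and the 85% power relates to a secondary outcome against traction alone

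*Protocol article*

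**What the plan says.** All of the following is in the protocol article.

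- **Inputs (Sample Size Calculation).** The calculation rests on the visual analog scale. It cites that "patients with LDH had a score of 4.28 (SD 1.16) points after Tuina intervention" and "a score of 5.68 (SD 1.26) points after traction intervention".
- **Error rates (same section).** "We used G*Power 3.1 software to calculate the sample size based on the mean, wherein α is .05 and power is .85". The Statistical Analysis section makes the test two-sided at .05 and assigns the Mann-Whitney test to between-group comparisons of SF-MPQ scores.
- **Result (Sample Size Calculation).** "Each of the 2 groups require 30 cases. With 20% dropout, 38 cases are required for each group for a total of 72 cases".
- **Total elsewhere.** Trial Design: "A total of 76 eligible patients with LDH will be recruited for this trial". The Abstract also gives seventy-six.
- **Outcomes.** Outcome Measurements: "fMRI will be used for the main measurements". The SF-MPQ is secondary, and its own section lists the visual analog scale as one of five indicators.
- **Control arm.** Trial Design and Conclusions describe it as TENS combined with traction.
- **fMRI sizing.** Sample Size Calculation says that no consensus exists and cites a literature figure: at least 24 participants for 80% power at single-voxel level.

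**The concern.** A sample-size paragraph should let a reader go from inputs to result. This one prints every input and the software, yet a difference larger than one standard deviation should not need 30 per group at 85% power. The total also disagrees with the per-group number in the same sentence.

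There is a question of scope as well. The only power figure calculated for this trial belongs to a component of a secondary outcome, and it uses a comparator that is only part of the actual control treatment. The trial will be reported against this paragraph. If it stands, the report will carry a wrong requirement, a wrong total, and a power figure that says nothing about the primary comparison.

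**Working it through.** **Inputs.** From Sample Size Calculation: means 4.28 and 5.68, SDs 1.16 and 1.26, alpha .05, power .85, dropout 20%. From Statistical Analysis: two-sided testing. From Trial Design: 1:1 allocation.

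**1. Effect size.**
- Difference = 5.68 − 4.28 = 1.40.
- Pooled SD = √[(1.16² + 1.26²)/2] = √1.4666 = 1.211.
- d = 1.40/1.211 = 1.156.

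**2. Trying to reproduce 30 per group.**

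Normal approximation: n = 2(z₀.₉₇₅ + z₀.₈₅)²/d² = 2(1.960 + 1.036)²/1.156² = 13.4, so 14 per group.

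Noncentral t (the two-sample t test for means), with noncentrality d√(n/2) and 2n − 2 degrees of freedom:

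| n per group | Noncentrality | Power |
|---|---|---|
| 14 | 3.06 | 0.837 |
| 15 | 3.17 | 0.863 |
| 30 | 4.48 | 0.993 |

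So 15 per group are needed. The stated 30 does not reproduce.

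Other ways to set up the calculation at alpha .05 and power .85:

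| Variant | n per group |
|---|---|
| t test, one-sided | 12 |
| t test, two-sided, SD 1.16 in both groups | 14 |
| t test, two-sided, SD 1.26 in both groups | 16 |
| Mann-Whitney, relative efficiency 0.955 | 16 |
| Mann-Whitney, relative efficiency 0.864 | 17 |

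A simulation of the Mann-Whitney test with normal data at the cited means and SDs (4,000 runs) gave power 0.836, 0.866 and 0.889 at 15, 16 and 17 per group. None of these variants comes near 30.

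**3. What 30 per group does provide.** By two-sided t test at .05, 85% power with 30 per group corresponds to d = 0.787. With SD 1.211 the detectable difference is 0.787 × 1.211 = 0.953, or about 0.95 points.

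**4. Dropout and total.**
- 30/(1 − 0.20) = 37.5, rounded up to 38. This reproduces.
- 2 × 38 = 76. The stated 72 does not reproduce; the 76 in the Abstract and Trial Design does.

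**5. Scope of the 85%.**

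| | Basis of the calculation | The trial |
|---|---|---|
| Outcome | VAS, one of five indicators of a secondary outcome | fMRI is primary |
| Comparator | Traction | TENS with traction |

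The document gives no between-group fMRI effect, so power for the primary comparison cannot be computed from it. The 24-participant figure is a separate literature reference at 80% power and is not the source of the 30 or the 85%.

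**The case against.** The strongest reply is that the consequences are small. For the contrast that was sized, the error is conservative: 30 evaluable per group give more power than claimed. The enrolment target is 76 in both other places, and the per-group 38 in the faulty sentence already points to it, so 72 is an isolated slip. Sizing an imaging trial on a pain score, alongside an imaging rule of thumb, is an openly declared choice. All of this stands. It limits the consequence but does not make the printed figures right. Nor is this a matter of journal condensation, because the inputs, error rates, result and total are all printed and disagree.

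Several stronger readings are tempting, and the document does not support them:

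- **That the plan claims 85% power for fMRI.** It does not. The section treats fMRI first and separately, then names the VAS, gives its means and SDs, and only then states the power.
- **That the trial is underpowered against its real control.** TENS could narrow the difference, but the document gives no figure. For assumed differences of 1.0, 0.7 and 0.5 points, with SD 1.21 and 30 per group, power would be 0.88, 0.60 and 0.35. That shows sensitivity, not a demonstrated shortfall.
- **That the 30 is the two-group total (2 × 15) misread as a per-group number.** The numbers coincide, but nothing in the text shows how the 30 arose.
- **That a detectable fMRI effect can be quoted.** This would need a voxel-level threshold, and the document does not fix one.

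**Conclusion.** The point holds as an error in the printed figures. The cited inputs require 15 per group by t test, or about 16 to 17 by Mann-Whitney, so the stated 30 is about twice the requirement. At 30 evaluable per group, power for the cited difference is 0.993 rather than 0.85. The total is understated by 4 (72 against 76).

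The stated power applies only to the VAS with traction-alone inputs. It carries over neither to the TENS-with-traction control nor to the primary fMRI outcome. The inflation from 30 to 38 and the enrolment target of 76 are correct, and no shortfall in enrolment follows.

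The t-test figures assume roughly normal scores and the pooled SD of 1.211. The Mann-Whitney range assumes relative efficiency between 0.864 and 0.955. The mismatch in total and the limits of scope rest on no assumption.

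**What to change.** Keep enrolment at 76 and rewrite the Sample Size Calculation paragraph so that it:

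1. gives the total as 76 (38 per group);
2. states that the cited VAS inputs need 15 per group at two-sided .05 and 85% power by t test;
3. states that 30 evaluable per group give about 99% power for a 1.4-point difference, or 85% power for about 0.95 points (t test, SD 1.21);
4. states that the calculation applies to the secondary VAS outcome, uses inputs from traction alone, and establishes no power for the primary fMRI comparison.

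The cost is one rewritten paragraph, with no change to enrolment, conduct or analysis. The price is candour: the stated justification becomes less favourable for the primary outcome, since only the literature figure of 24 participants would remain in its support.
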